### Randomization and concealed allocation

The randomization of the study will be performed by a researcher not involved in the recruitment of participants ([name]), using Microsoft Excel for Windows. Allocation will be concealed and sealed in opaque envelopes in consecutively numbered sequences. Participants will be randomized to either the Aerobic Group or the Pilates Group.

### Interventions

Both groups will receive education through an educational booklet with information on fibromyalgia, central sensitization, self-care strategies for pain management and fatigue reduction (such as graduating activities of daily living and use of self-massage), improved sleep (such as avoiding caffeine and cigarette, and watching TV one hour before bedtime), improved depression and stress management (such as practicing physical activity and performing psychotherapy) [42, 43]. The booklet will also provide information about the importance of exercise in the management of fibromyalgia and delayed onset muscle soreness to reduce fear and avoidance of patients in relation to the practice of exercises. The participants may continue to use the medications prescribed by their doctor. The treatment will be carried out in person for eight weeks, with 16 individually tailored sessions lasting 60 min each. At each session, the participants will rate their pain before and after exercise. Any adverse effects caused by the exercises will be noted daily.

The Aerobic Group will perform aerobic exercises, and the training heart rate (HR) will be 57 to 76% of maximum heart rate (HRmax), which corresponds to the mild to moderate exercise intensity indicated for these patients [16, 25, 44]. HRmax will be calculated indirectly by the equation for maximum predicted heart rate by age (HRmax = 208–0.7 x age) [45, 46]. Patients should maintain training HR, which will be monitored by the frequencymeter, and a perceived effort between 11 and 13 (considered mild to moderate) [47] on the Borg scale [48]. The Borg scale will be the main factor considered when changing the intensity of the exercise if the patient presents a high perceived exertion and still does not reach the training HR. The indirect prescription of HRmax was chosen because it has been validated for sedentary patients with fibromyalgia and because it shows good correlation (*r* = 0.642; *p* < 0.05) with the HRmax obtained through ergospirometry [45]. The aerobic exercises will be done on a treadmill (model LX 3.0) or stationary bicycle (models LXU and LXR, Movement Fitness Equipment, Sao Paulo, SP, Brazil). The choice of treadmill or bicycle will be based on the comorbidities and preferences of the participant, because there are no differences between various aerobic exercise modalities in improving clinical outcomes in patients with fibromyalgia [14, 16, 17], and the chosen modality will be maintained until the end of the treatment [16]. The sessions will start with a warm-up (10-min walk) and will end with relaxation (10-min massage with a ball) with the patient lying down. The participants will be informed that they may have a tolerable increase in pain and fatigue in the short term, but these symptoms should return to baseline levels after the first weeks of exercise at adequate intensity [16]. The physical therapists responsible for aerobic exercise ([name] and [name]) have two and seven years of undergraduate training, specialization in Sports Physical Therapy and Musculoskeletal Physical Therapy, and experience with the prescription of aerobic exercises.

The Pilates Group will receive a specific Pilates exercise program based on a previously published exercise booklet [49] with the inclusion of a few new exercises (Additional file 1). The sessions will include mat exercises with accessories as well as equipment-based exercises (Cadillac, Reformer, Ladder Barrel, and Step Chair, Metalife, Sao José, SC, Brazil). The last 10 min of the session will also consist of relaxation with a ball massage. In the first session, the participants will receive instructions on the method and will be trained on powerhouse activation through isometric contraction of the transverse abdominal, multifidus, and pelvic floor muscles associated with expiration [50, 51]. The exercises of the modified Pilates method will be executed in three levels of difficulty: basic, intermediate, and advanced. This level of difficulty will be defined individually and the participant’s progress between the levels will depend on how well they do the 10 repetitions of the exercises without postural compensations [52, 53]. The physical therapists responsible for Pilates exercises ([name] and [name]) have six and ten years of undergraduate training, specialization in Musculoskeletal Physical Therapy, and seven and nine years of experience with the Pilates method.

The participants who are allocated to one group will not be transferred to the other group under any circumstances. If the participant is unable to perform the treatment after allocation, he will not do that specific exercise and will be reassessed according to the principles of intention-to-treat analysis. When the participants miss a session, the therapists will contact them by phone to schedule a make-up session. In these cases of absence, the 8-week protocol can be extended for up to 10 weeks to include the make-up sessions. All patients will receive refund for the money spent on public transportation to attend the treatment, which is a strategy to improve adherence in low income countries.

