## Discussion

Until the moment, this is the most robust and least biased study about the effectiveness of the Pilates method as a treatment resource for patients with fibromyalgia, comparing it with aerobic exercise. It is also the first study to investigate the cost-effectiveness of two different modalities of therapeutic exercise. Current evidence shows that aerobic exercise does not generate very good adherence in the treatment of patients with fibromyalgia [60], although it has a low to moderate effect on the improvement of their symptoms [16]. Pilates method can lead to greater adherence [61] because it uses equipment and exercises divided into levels of progression. Pilates exercises may cause less muscle soreness and may be more pleasurable and stimulating, which would facilitate its implementation in patients with fibromyalgia who tend to be resistant to exercise. Finally, there is little information on the long-term effects of different exercise modalities for patients with fibromyalgia, and this study will monitor these patients for one year.

This study aims to clarify whether the Pilates method can be incorporated into the clinical practice of physical therapists treating patients with fibromyalgia, as well as which exercises to use and how these exercises can be performed. An easy-to-replicate protocol for aerobic exercise in these patients, with adequate training intensity and frequency, will also be described, as well as information about muscle soreness pain and progression of exercises in each exercise modality. The study will also provide information on which exercise will be most cost-effective, information that can be used by insurers and public health systems. With this study, patients will know whether the Pilates method can be used as an alternative treatment and which exercise modality causes less pain.

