The study took all measures to minimize the risks of methodological bias, that is, it was prospectively registered, and it has a relevant sample, concealed allocation, intention-to-treat analysis, and blinded assessor. It allows generalization of the data for the majority of patients with fibromyalgia. In addition, it has pragmatic interventions, with Pilates exercises being performed as in clinical practice, with individualized exercises according to the clinical conditions of the participants each day, without a fixed protocol. The aerobic exercise will be prescribed following the recommendations of the most recent systematic reviews [16, 25] and the American College of Sports Medicine [44], respecting the individuality and clinical condition of each participant by monitoring exercise intensity. The physical therapists responsible for the interventions have clinical experience in the prescription of the respective exercises. The study has as a limitation the non-blinding of participants and therapists, and this limitation stems from the type of intervention (physical exercise).

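### Adverse effects are recorded only if judged to be caused by the exercises, which in an unblinded trial with separate therapists per group risks unequal recording of harms

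*Protocol article*

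**What the plan says.** All places are in the Protocol article.

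- **Recording rule.** Methods, Interventions, in the paragraph common to both groups: "Any adverse effects caused by the exercises will be noted daily". The article gives no rule for events not attributed to the exercises and does not say who decides on cause.
- **Session pain.** The same paragraph: "At each session, the participants will rate their pain before and after exercise". This applies to every participant and does not depend on attribution.
- **Blinding.** Discussion: "The study has as a limitation the non-blinding of participants and therapists". The Interventions section describes different physical therapists for the two groups.
- **Prior expectation.** Discussion: "Pilates exercises may cause less muscle soreness and may be more pleasurable and stimulating".
- **Information given to participants.** The common paragraph says "Both groups will receive education through an educational booklet", and the booklet carries "information about the importance of exercise in the management of fibromyalgia and delayed onset muscle soreness to reduce fear and avoidance". The Aerobic Group paragraph adds "The participants will be informed that they may have a tolerable increase in pain and fatigue in the short term", followed by the reassurance that "these symptoms should return to baseline levels after the first weeks of exercise at adequate intensity". The Pilates Group paragraph has no matching sentence.

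**The concern.** The rule makes causality a condition of entry to the record instead of a property noted about an event already in it. In fibromyalgia, pain and fatigue are the disease itself, so deciding whether a flare came from the exercise is largely a judgement. Here that judgement would be made by people who know the allocation, at sessions run by different staff in each group, in a team that has said in print that it expects less soreness with one of the two treatments. An event screened out at this stage is never written down, and no later analysis can recover it.

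What is at stake is the description of harms by group. The Discussion says that patients will learn which of the two kinds of exercise is less painful, and that soreness will be reported for each modality, so readers will compare the groups on tolerability even though no formal test of harms is stated.

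The secondary matter is information. If one group is told explicitly to expect more pain and fatigue for a while and the other is not, unblinded participants may report symptoms differently for a reason other than the exercise.

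**Working it through.** The article gives no adverse-event rate and no figure for attribution, so there is no stated figure to reproduce. The check sets the statements against each other and writes out what the rule does to a comparison.

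**1. What the filter does.** For group g, let N be the number randomised (49 in each group, Sample size calculation), r the true number of events per person, c the share of events that come to the notice of the person recording, and a the share of those that are attributed to the exercise. Then

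expected recorded events = N × r × c × a.

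With N equal, the ratio of recorded events, Aerobic to Pilates, is

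(r_A / r_P) × (c_A / c_P) × (a_A / a_P).

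The first factor is the quantity of interest. The other two are distortions. If both equal 1, the recorded ratio equals the true one, although the counts in both groups are still too low whenever a or c is below 1. The article gives no value for a or c, so the size and direction of any distortion are unknown.

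**2. Is there reason to doubt that a_A = a_P?** The wording of the rule is the same for both groups. Its application rests on a judgement for which no assessor is named, with unblinded therapists and participants, separate therapists per group, and a stated expectation favouring Pilates on soreness. Equality is possible, but nothing in the described procedure secures it.

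**3. Is there reason to doubt that c_A = c_P?** Sixteen sessions in eight weeks leave 8 × 7 − 16 = 40 days without a session. With the permitted extension to 10 weeks it is 10 × 7 − 16 = 54 days. The word daily therefore most naturally means session days. A participant who attends can report at the next session what happened in between. For one who misses or stops, the described contacts are:

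- the telephone call after a missed session, whose stated purpose is to arrange a replacement;
- the follow-up assessments, whose listed questions cover medication, physical activity and other treatment, with satisfaction added at eight weeks.

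Adverse events are not named at either contact. The Discussion reports poor adherence to aerobic exercise and suggests that Pilates may do better, so attendance, and with it capture, could differ by group. The article does not say that events go unrecorded at these contacts, so non-capture is an inference.

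**4. Which outcomes does the filter touch?** It touches the adverse-effect record only. Pain before and after each session is rated by everyone, so those ratings, and the planned survival analysis of sessions to a 30% pain reduction if it uses them, carry no causality condition. The Fibromyalgia Impact Questionnaire is likewise collected regardless of attribution.

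**5. Information by group.**

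| Item | Aerobic Group | Pilates Group |
|---|---|---|
| Booklet covering delayed onset muscle soreness | yes | yes |
| Explicit notice of a short-term rise in pain and fatigue | stated | not stated |
| Reassurance that this should pass | stated | not stated |

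The notice refers to the participants in general terms, but it stands in the Aerobic Group paragraph. The documents do not settle whether Pilates participants hear the same.

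**The case against.** The strongest case on the other side has five parts.

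- **One rule applies to both groups, and differential attribution is nowhere shown.** This stands. A reader might infer that the comparison of harms is biased; the documents support a risk of bias and no more. It is also not stated that the therapists make the attribution.
- **Adverse effects are neither a primary nor a secondary outcome, and no between-group analysis of harms is stated.** This stands and limits the consequence. It does not remove it, because the Discussion promises patients information on how painful each modality is. The pain ratings that chiefly serve that promise are free of the filter.
- **An article leaves adverse-event forms and definitions to the full protocol.** That is fair for definitions and forms, and for what is asked by telephone. It does not cover the recording rule, which the article states in restrictive words.
- **Participants in both groups are prepared for soreness.** This stands. A reader might infer that only the Aerobic Group is told to expect more pain; the shared booklet contradicts that. What differs in the text is the additional explicit notice on pain and fatigue. Its effect could run either way: it might raise reported pain, or make pain seem normal and reduce reports. Because the message says that symptoms settle after the first weeks, it bears less on the primary outcome at eight weeks than on the early session ratings.
- **Modality-specific advice can be part of a pragmatic intervention.** This stands, so identical information for both groups is a choice and not a requirement.

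**Conclusion.** The point holds as a risk arising from the stated rule. Recording is limited to effects attributed to the exercises, in an unblinded trial with separate therapists per group and no named assessor of cause, so harms may be recorded unequally. Events in participants who miss sessions may not be captured. No numerical size can be given, since any ratio would only restate attribution and capture rates that the documents do not supply. The primary outcome and the session pain ratings are not affected by the filter. The conclusion assumes that the recording rule means what it literally says and that the full protocol does not already collect all events.

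The information given to the groups is a secondary point of clarity: the common paragraph and the two group paragraphs of the Interventions section need to be reconciled. The change is worth making because unlogged events cannot be recovered later and the remedy is cheap.

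**What to change.** 1. Replace the recording rule with one that covers all adverse events in both groups, whatever their cause. Ask the same open question in both groups at each session, at the telephone call after a missed session, and at the eight-week visit.
2. Record relatedness to the exercise in a separate field, and say who judges it.
3. Summarise all events by group, with those judged related shown as a subset.
4. Reconcile the common, Aerobic Group and Pilates Group paragraphs by stating whether both groups receive the same information on short-term symptoms. The content, and whether it should be the same, is for the clinical investigators. If it differs by design, say so and note it when interpreting self-reported pain.

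The cost is one common form with one question, used at contacts already planned, and one or two clarifying sentences. The downside is that more unrelated events will be logged and will need to be summarised. No visit and no participant is added.

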### Statistical analysis

All assessment forms will be scanned and stored in a safe place, and data tabulation will be saved on the study’s computer and on pen drives to avoid losses. The participants will be coded by numbers to maintain the confidentiality of their personal data, which will not be disclosed. One of the researchers ([name]) will certify the data collection stage. The final results of the study will only be revealed upon completion of all follow-ups, and only the authors of the article will have access to the data prior to publication.

The data will be entered twice to avoid tabulation errors, and the statistician will receive the coded data and will be blind to group allocation. In both groups, descriptive analysis and evaluation of data normality will be performed through the visual inspection of histograms. The mean effects of the interventions and the differences between groups for all outcomes will be calculated using linear mixed models, which incorporate terms for the treatment groups, time (follow-ups), and interaction terms (treatment groups versus time). Time will be coded as a categorical variable (i.e., four variables will be created for the category baseline, eight weeks, six months, and 12 months). Treatment coefficients versus time interactions will be equivalent to the estimates of the differences between groups. The statistical analysis will use the software SPSS 19 for Windows.

The cost-effectiveness analysis will be performed using the impact of fibromyalgia as outcome, and the cost-utility analysis using QALYs. Mean between-group cost differences will be calculated for total and disaggregated costs. Seemingly unrelated regression analyses will be performed in which effect and cost differences will be corrected for their baseline values if available, while also taking into account the possible correlation between effects and costs [54]. Incremental cost-effectiveness and cost-utility ratios will be calculated by dividing the corrected difference in total costs by the difference in effects. Uncertainty surrounding the cost differences and incremental cost-effectiveness and cost-utility ratios will be estimated using Bias Corrected and Accelerated bootstrapping techniques (5000 replications). The latter will be graphically presented in cost-effectiveness planes [55]. Cost-effectiveness acceptability curves will be estimated to indicate the intervention’ probability of being cost-effective compared with other at different values of willingness-to-pay [56]. The economic evaluation will be performed using STATA V.14.

In addition, a survival analysis will be performed to evaluate the number of sessions necessary for a 30% pain reduction compared to the initial pain, and this value was chosen because it is considered a minimal clinically significant difference in pain in patients with fibromyalgia [57]. This analysis will be performed using the Kaplan-Meier method [58] and the comparison between the groups by the Log-Rank test [59]. All analyses will follow the intention-to-treat principle. The significance level will be set at 5%. Table 3 shows the timeline of the study.

**Table 3 Tab3:** Timeline for the schedule of enrollment, interventions, and assessments

Outcomes	Enrollment	Before randomization	Intervention period (8 weeks)	8-week follow-up after randomization	6-month follow-up after randomization	12-month follow-up after randomization
Eligibility criteria	X					
Demographic data	X					
Informed consent	X					
Primary outcome						
Fibromyalgia impact		X		X		
Secondary outcomes						
Fibromyalgia impact					X	X
Pain intensity	X	X	X	X	X	X
Kinesiophobia		X		X	X	X
Specific disability		X		X	X	X
Health-related quality of life		X		X	X	X
Sleep quality		X		X	X	X
Functional capacity		X		X		
Interventions						
Aerobic exercise			X			
Pilates exercise			X			

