### Sample size calculation

The study was designed to detect a clinically significant 8 points (14%) difference in the impact of fibromyalgia assessed by the Fibromyalgia Impact Questionnaire eight weeks after randomization (estimated standard deviation = 12), assuming α = 0.05, statistical power of 80%, and loss to follow-up of 15%. This value represents the minimal clinically important difference [26]. The sample size calculation resulted in a sample of 98 participants divided into two groups of 49 each. To reach this number, the study will be promoted in community newspapers and on the internet.

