### Assessment of clinical outcomes

Before baseline assessment, the participants will give consent and sign the Informed Consent Form. A blinded assessor will confirm the eligibility criteria and the diagnosis of fibromyalgia through the criteria of the American College of Rheumatology 2010 [2]. Next, demographic and anthropometric data will be collected, as well as information on the use of medications (type and quantity) for fibromyalgia and physical therapy or other previous treatment. Finally, the participants will be assessed for the primary and secondary outcomes. The assessments will be performed at baseline, eight weeks, six months, and 12 months after randomization, and in the last three assessments, the patients will be instructed not to provide information about their treatment to the blinded assessor. In the follow-ups assessments, patients will also be asked about the use of medication and physical activity or other treatment for fibromyalgia. The baseline and eight-week assessments will be face-to-face, and the six- and twelve-month assessments will be conducted over the phone to minimize loss to follow-up. In the eight-week assessment patients will also be asked about their satisfaction with the treatment. All of the scales and the questionnaire used in this study have already been translated and adapted to Brazilian Portuguese [29–41].

The primary outcome is the impact of fibromyalgia eight weeks after randomization. The secondary outcomes are: impact of fibromyalgia six and 12 months after randomization; pain intensity, kinesiophobia, sleep quality, health-related quality of life and specific disability eight weeks, six months, and 12 months after randomization; pain intensity at each session, before and after treatment; and functional capacity eight weeks after randomization (Table 1).

**Table 1 Tab1:** Description of the outcome measures

Measure	Construct	Description

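### The planned mixed model leaves the baseline group difference free, so its 8-week effect is a valid but needlessly imprecise unadjusted difference in change

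*Protocol article*

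**What the plan says.** The protocol article, Statistical analysis, specifies "linear mixed models, which incorporate terms for the treatment groups, time (follow-ups), and interaction terms (treatment groups versus time"). Time is categorical: "four variables will be created for the category baseline, eight weeks, six months, and 12 months". Baseline FIQ is therefore part of the response, and the group term is free. Neither a baseline covariate nor a common baseline mean is mentioned. The section then identifies the effect estimate: "Treatment coefficients versus time interactions will be equivalent to the estimates of the differences between groups". The reference time level is not named.

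Assessment of clinical outcomes fixes the endpoint: "The primary outcome is the impact of fibromyalgia eight weeks after randomization". Sample size calculation states: "The study was designed to detect a clinically significant 8 points (14%) difference in the impact of fibromyalgia", with "estimated standard deviation = 12", "assuming α = 0.05, statistical power of 80%, and loss to follow-up of 15" per cent. It does not say whether the SD is that of scores or of change.

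For the economic evaluation, the same Statistical analysis section says that "effect and cost differences will be corrected for their baseline values if available".

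**The concern.** With baseline as the reference level, the coefficients mean the following:

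- group term: the difference between groups at baseline;
- 8-week interaction: change in the Pilates Group minus change in the Aerobic Group;
- 8-week difference between groups: group term plus interaction.

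In a randomised trial the true baseline difference is zero. Estimating it as a free parameter adds the noise of the baseline comparison to the primary effect. The baseline FIQ scores that would remove most of this noise are already collected. At stake are the width of the primary confidence interval and, if baseline and 8-week scores correlate weakly, the stated power. A chance baseline imbalance also passes in full into the gap between the coefficient and the observed 8-week difference.

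**Working it through.** **Inputs from the protocol article.** Difference 8 FIQ points, SD 12, alpha 0.05, power 80%, loss 15%, 49 per group (Sample size calculation).

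**Assumptions.** Two-sided test; 42 followed per arm (49 × 0.85 = 41.65); equal SD at every visit; the same correlation ρ between any two visits (compound symmetry). The documents give no ρ, so a range is shown.

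**The plan's own figure.** n per arm = 2(1.96 + 0.84)² × 12²/8² = 35.3, so 36. Then 36/0.85 = 42.4, so 43 per arm and 86 in total (88 with the exact t-test). The stated 98 is larger. It matches 85% power: 2(1.96 + 1.04)² × 12²/8² gives 41, and 41/0.85 gives 49 per arm. The extra patients are a cushion in what follows.

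**Variance of the 8-week contrast.** Generalised least squares for the four-visit model, with 49 baselines and 42 followed per arm, gives:

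- planned (free baseline difference): 2 × 144 × [(1 − ρ²)/42 + (1 − ρ)²/49];
- common baseline mean: 2 × 144 × (1 − ρ²)/42.

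The second term of the first line is the cost of estimating a baseline difference known to be zero. It is positive for every ρ below 1.

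Example at ρ = 0.5. Planned: 288 × (0.75/42 + 0.25/49) = 5.143 + 1.469 = 6.61. Common baseline: 5.14. Ratio 1.29.

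| ρ | SE planned | SE common baseline | Variance ratio | Power planned | Power common baseline |
|---|---|---|---|---|---|
| 0.3 | 3.02 | 2.50 | 1.46 | 74.5% | 89% |
| 0.4 | 2.81 | 2.40 | 1.37 | 80.4% | 91% |
| 0.5 | 2.57 | 2.27 | 1.29 | 86.7% | 94% |
| 0.7 | 2.01 | 1.87 | 1.15 | 97.6% | 99% |

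Power is from the noncentral t with 82 degrees of freedom and a true difference of 8. Planned power equals 80% at ρ = 0.39.

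**If SD 12 is the SD of change.** SE = 12 × √(2/42) = 2.62 and planned power is about 86%. Baseline adjustment would give about 91% (ρ = 0.7) to 97% (ρ = 0.3).

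**Bias.** In simulations of both models with a true effect of −8 and 15% loss, the mean estimates at ρ = 0.3, 0.5 and 0.7 were −7.84, −8.20 and −8.02 (free) and −7.83, −8.14 and −8.01 (common baseline). Neither is biased.

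**Chance imbalance.** The SE of the baseline difference is 12 × √(2/49) = 2.42. An imbalance of 3 points or more in either direction (3/2.42 = 1.24 SE) has probability about 0.22. With complete data, a 3-point imbalance puts the interaction coefficient 3 points from the observed 8-week difference and (1 − ρ) × 3 = 1.5 points from the adjusted estimate at ρ = 0.5.

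**The case against.** The strongest reply is that the plan is valid as written, and that stands. Three stronger readings are tempting, and the documents support none of them.

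- **Wrong estimand.** A reader might infer that the interaction does not estimate the difference between groups at all. Under randomisation the difference in change has the same expectation as the 8-week difference. The protocol never calls the coefficients baseline-adjusted. The adjusted estimate does not equal the observed 8-week difference either: with a 3-point imbalance and ρ = 0.5 it too is 1.5 points away. The sentence is loose, and the issue is efficiency.
- **Underpowered trial.** This needs two things the documents do not state: that 12 is the SD of scores, and that ρ is below about 0.39. A simple completers-only change-score formula would put the limit at about 0.42 and the variance ratios at 2/(1 + ρ). But the planned mixed model also uses the baselines of patients lost to follow-up, so that formula overstates the loss.
- **Two conflicting FIQ effects.** The economic regression corrects for baseline, but the text gives no FIQ time point for it and its purpose is different. It is not shown to re-estimate the 8-week primary contrast, so no contradiction is established.

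Two further replies hold in part. A change contrast is not always a poor choice: in the simple complete-data comparison it beats an unadjusted 8-week comparison when ρ exceeds 0.5. Covariance structure and reference level are details an article may leave to a fuller plan. Here, however, the article itself lists the model terms and says which coefficients are the effect, so the choice of a free baseline difference is made in the text and can be commented on.

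**Conclusion.** The point holds as an efficiency point. On the natural reading, the primary effect is an unadjusted difference in change: unbiased, but less precise than the collected data allow at every correlation below 1. The excess variance is about 15% to 46% for ρ from 0.7 to 0.3, given SD 12 for scores, compound symmetry, 49 baselines and 42 followed per arm. The loss is small when ρ is high. A miss of the stated 80% power is a conditional possibility only. The interpretation depends on baseline being the reference level; with another reference the interaction coefficients would mean something else, which is a reason to state it. This is a free improvement and not a must-fix.

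**What to change.** Either of two changes to the Statistical analysis section is enough:

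1. Drop the treatment main effect so that the two groups share one baseline mean, and keep treatment-by-time terms at 8 weeks, 6 months and 12 months only, with an unstructured covariance.
2. Take baseline out of the response and enter it as a covariate, with its own coefficient at each follow-up.

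In both cases add that the 8-week treatment coefficient is the primary contrast. The coefficients are then baseline-adjusted differences between groups at each visit, and the clinical analysis follows the baseline-correction principle that the economic regression already uses.

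The cost is about two sentences and one changed model line, with no new data. The change should be made before anyone sees results by group, so that the choice of estimate cannot depend on them.
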